#### Adverse events and monitoring safety

All unexpected adverse events related to CKJ pills intake will be reported to the investigator by participants and write on the individual case report form by the investigator. Safety will be assessed by the reporting of clinical laboratory tests, vital sign measurements, and adverse events. Clinical laboratory tests, including AST/ALT, BUN/creatinine, red blood cell (RBC) count, white blood cell (WBC) count, hemoglobin, hematocrit, number of platelets, and number of differentiated cells will be determined at weeks 0 (baseline) and 12 (end of the trial). Vital signs of each participant will be checked with monitoring of adverse events (nausea/vomiting, fatigue, allergic reaction, and any adverse events related to CKJ pills) after each visit.

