Histamine is one of the important mediators that elicit a variety of symptoms such as wheal and flare response. Since these histamine-related symptoms provoke the urge to scratch, often impairing the quality of life, measures to suppress and control these symptoms are required. In the development of a new anti-histamine, the histamine-induced wheal and flare skin test has been used most frequently. The histamine-induced wheal and flare test is based on the measurement of local swelling caused by plasma extravasation (wheal) and reflex vasodilatation (flare) after histamine challenge [17]. Therefore, the histamine skin prick test may be useful for assessing aspects of drug activity during the early clinical development of a new anti-histamine.

The aim of this study is to evaluate the efficacy and safety of the CKJ, a dietary supplement for the treatment of allergic skin symptoms. This study will be first pilot study about the improvement of skin hypersensitivity reaction of the CKJ in healthy volunteers. The results of this study will give us the clinical of biochemical parameters such as IgE, histamine, and cytokines between the placebo and CKJ groups. On the basis of the results, we will suggest the optimal design, precise sample size, and primary outcome for a further large scale RCT.

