### Randomization

After enrollment, participants will be randomly assigned to one of the two groups, either the CKJ pills group or placebo pills group. The allocation ratio will be 1:1 in blocks of 2. Randomization will be performed at a site remote from trial location. Random numbers will be generated by a computerized random-number generator through the block-randomization method of a software program (Excel, Microsoft Office 2007) for sequence generation. At the time of randomization participants will draw an envelope. Each envelope contains a number that is concealed to the treatment allocation. Randomization sequence and allocation will be concealed to all study subjects, research staff, investigators and pharmacists until completion of the study. The allocation list will be protected by password access files and held by a non-investigator independent. In the event of an emergency medical situation the individual's randomization code and group allocation can be identify.

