#### Secondary outcomes

Secondary outcomes will be shown by the mean change of IgE, histamine, eosinophil cationic protein, IFN-gamma, IL-4, IL-10, and TNF-alpha. These biomarkers will be checked at weeks 0 (baseline) and 12 (end of the trial). The schedule of assessments is presented in Table 1.

**Table 1 T1:** A brief study schedule at every visit

	*Screening Visit 1*	*Baseline Visit 2*	*Visit 3*	*Visit 4*	*Visit 5*	*Follow up (Visit 6)*
	
	*D-21 ~D-1*	*Week 0 D0*	*Week 4 D28*	*Week 8 D56*	*Week 12 D84*	*Week 16 D112*
***Informed consent form***	◯					

***Demographic information taking***^***1***^	◯					

***Medical history taking***	◯					

***Inclusion/exclusion criteria check***	◯	◯				

***Physician examination***^***2***^	◯				◯	

***Drinking/smoking taking status***^***3***^	◯				◯	

***Vital sign measurement***	◯	◯	◯	◯	◯	

***Concomitant drugs check***	◯	◯	◯	◯	◯	

***Electrocardiogram(ECG)***	◯				◯	

***Histamine skin prick test***	◯				◯	

***Laboratory test***^***4***^	◯				◯	

***Histamine & ECP***		◯			◯	

***Study product distribution***		◯	◯	◯		

***Compliance checking***			◯	◯	◯	

***Adverse event monitoring***			◯	◯	◯	◯

***Diet, physical exercise counseling***^***5***^		◯	◯	◯		

◯ *: Item need to be performed during the visit*

^1 ^*Sex, date of birth, age, contact address and phone number*

^2 ^*Include present illness, past history taking*

^3,5 ^*Risk factors such as alcohol drinking, smoking, severe exercise and other dietary supplement intake will be managed*

^4 ^*Blood test(WBC, RBC, hemoglobin, hematocrit, platelets count, AST, ALT, ALP, gamma-GTP, albumin, BUN, creatinine, glucose, total bilirubin, total protein, total-cholesterol, triglyceride, LDL-C, HDL-C, IgE), urine test(specific gravity, pH, Protein, Ketone, Glucose, bilirubin, urobilinogen, nitrite, microscopic (RBC, WBC))*

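### The stated rule for entering adverse events on the case report form admits only unexpected, CKJ-related events; it conflicts with the wider monitoring described elsewhere and risks under-counting in both arms

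*Protocol article*

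**What the plan says.** The Background makes safety part of the purpose of the trial: "The aim of this study is to evaluate the efficacy and safety of the CKJ".

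The section on adverse events and safety monitoring then makes three statements that differ in scope:

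- Entry on the form: "All unexpected adverse events related to CKJ pills intake will be reported to the investigator by participants", after which the investigator enters them on the case report form.
- What safety rests on: "Safety will be assessed by the reporting of clinical laboratory tests, vital sign measurements, and adverse events". Here adverse events carry no qualifier.
- What is followed at visits: "monitoring of adverse events (nausea/vomiting, fatigue, allergic reaction, and any adverse events related to CKJ pills) after each visit".

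Table 1, under Secondary outcomes, has a row "Adverse event monitoring", again unqualified, marked at Visits 3 to 6 (weeks 4, 8, 12 and 16). The Randomization section keeps the trial blind throughout: "Randomization sequence and allocation will be concealed to all study subjects, research staff, investigators and pharmacists until completion of the study".

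**The concern.** The entry rule sets two conditions before an event becomes data: it must be unexpected, and it must be related to CKJ. Both are judgements about individual cases. A placebo-controlled trial is meant to make such judgements unnecessary, because the comparison of event rates between randomised groups shows whether the product causes harm. This is described as the first pilot study of CKJ for skin hypersensitivity, so there is little experience on which to decide what is expected or attributable.

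A harm that nobody recognises as product-related is the kind that such a filter drops. An event never written down cannot be restored by any later analysis plan, so this is a defect in a stated data-collection rule and not a detail left for another document. At stake are the completeness of the adverse event counts and the safety information that the pilot hands to the larger trial announced in the Discussion.

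**Working it through.** The plan gives no figure on this point, so the check is mainly a comparison of the statements, followed by an illustration of size.

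**Step 1: which events reach the form?** Each type of event is set against the entry rule and the visit monitoring.

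| Type of event | Entry rule | Visit monitoring | Result |
|---|---|---|---|
| Nausea/vomiting, fatigue, allergic reaction | Arguably excluded: an event listed in advance is hardly unexpected | Included, no filter | Monitored; unclear whether it is entered on the form |
| Other event, unexpected and judged related | Included | Included | Recorded |
| Other event, judged related but expected | Excluded | Included | Monitored; unclear whether it is entered on the form |
| Other event, judged unrelated | Excluded | Excluded by the catch-all | Lost, if the text is followed as written |

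The unqualified sentence on the safety assessment and the unqualified row in Table 1 would cover all four types. The statements therefore do not agree, and the narrowest is the only one that mentions the form.

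**Step 2: does the filter differ by arm?** Participants, staff and investigators are all blinded until completion. A judgement made without knowledge of allocation should keep about the same fraction c of events in each arm. With true rates p1 and p0, the recorded rates are c·p1 and c·p0, and the recorded difference is c·(p1 − p0). Both rates are understated and the difference shrinks by the factor c. Its direction is unchanged.

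**Step 3: chance that an event is not seen at all in one arm.** The inputs are n = 30 per arm (60 participants allocated 1:1, from the Recruitment and Randomization sections), a true event rate of 10% (assumption) and a capture fraction c (assumption, varied). The formula is P(none recorded) = (1 − 0.10·c)^30.

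- c = 1: 0.90^30 = 4.2%
- c = 0.75: 0.925^30 = 9.6%
- c = 0.50: 0.95^30 = 21.5%

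**Step 4: effect on a comparison.** Take true rates of 10% and 40% (assumption), 30 per arm, and a two-sided 5% test of two proportions by the normal approximation with the pooled variance under the null.

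- c = 1 (10% v 40%): power 78%
- c = 0.50 (5% v 20%): power 42%

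The rates and capture fractions in Steps 3 and 4 are not in the document. They show how quickly information is lost, not how much will be lost in this trial.

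**The case against.** The strongest case on the other side has five parts.

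- **The text does not say that other events are left off.** Visit monitoring names three events without any filter, and Table 1 applies to everyone. This stands in part. It rules out the reading that the only source is spontaneous participant report of unexpected, related events. It does not rescue other events judged unrelated, because the catch-all repeats the relatedness condition.
- **A reader might infer that placebo participants can have no recordable event, since they take no CKJ.** The documents do not support this. The Compliance section uses CKJ pills for the pills that participants return and applies the 70% threshold to them. In a blinded trial that has to mean the study product in either arm. Both filters remain even on this looser reading.
- **A reader might infer that the arms cannot be compared fairly.** This does not follow either. With allocation concealed from everyone who applies the filter, it should act alike in both arms. Laboratory tests, vital signs and the electrocardiogram are also collected from all participants whatever the suspected cause. What remains is loss of information, and those measurements do not capture symptoms.
- **Safety is not among the listed primary or secondary objectives, and firm conclusions are deferred to a full-scale trial.** This is true and limits the weight of the point. But the Background names safety as an aim, and the pilot is meant to be groundwork for that later trial.
- **A journal article condenses the protocol.** Detailed form instructions may well sit elsewhere, and their absence would be no finding. Here, however, a rule is stated, and it is the narrow one.

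**Conclusion.** The point holds as one of under-ascertainment and internal inconsistency. The only stated rule for the case report form, and the catch-all in the visit monitoring, filter events by attribution to CKJ; the entry rule also filters by expectedness. This conflicts with the unqualified safety assessment in the same section and with Table 1. Followed as written, other events judged unrelated are lost, and the route to the form is unclear for the named events and for other related events thought to be expected.

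The size depends on the fraction of events captured, which the document does not give. For an assumed 10% event in 30 participants, the chance of recording none rises from 4% at full capture to 10% at 75% and 21% at 50%. Those figures concern one arm and do not apply to the named events if monitoring brings them onto the form. Between arms, the recorded difference is diluted in proportion to capture, provided that blinding holds and capture is equal. Bias between arms would need a failure of blinding, which nothing in the document indicates.

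**What to change.** Replace the entry rule and the catch-all with a single rule: every adverse event in both arms is recorded on the case report form at the visits already scheduled, through week 16, whatever its expectedness or suspected relation. Record relation to study product (not to CKJ) as a separate field, judged under blinding. Tabulate all events by randomised group. Make clear that nausea/vomiting, fatigue and allergic reaction are entered in the same way.

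The cost is a change of wording in the protocol and the form, and slightly more event entry at visits that take place anyway. It should be made before enrolment, since events that were never recorded are hard to recover.

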#### Compliance

The CKJ pills remaining after each visit will be quantified in order to enhance medication compliance. Participants whose compliance with the CKJ pills is ≤ 70% of the total dose will be considered to have dropped-out.

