#### Sample size

Sample size calculation is performed; primary outcome measure will be the histamine-induced wheal size, whereby 5.0 square millimeters is assumed a clinically relevant difference between the two groups, with a standard deviation of 6.85, alpha set on 5% and power on 80%. This resulted in a required number of 24 subjects in each group. Assuming a dropout rate of 20%, a total of 60 subjects will be enrolled in this trial.

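### Counting participants with 70% compliance or less as drop-outs leaves the primary comparison open to bias, because nothing in the protocol keeps them in it

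*Protocol article*

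**What the plan says.** The Compliance section, which sits under Statistical analysis, describes a pill count: "The CKJ pills remaining after each visit will be quantified in order to enhance medication compliance". It then sets a threshold. The rule opens "Participants whose compliance with the CKJ pills is" and applies to those at or below "70% of the total dose will be considered to have dropped-out". Table 1 places compliance checks at Visits 3 to 5, all after randomisation.

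The Sample size section shows how drop-outs are treated in planning: "This resulted in a required number of 24 subjects in each group", followed by "Assuming a dropout rate of 20%, a total of 60 subjects will be enrolled in this trial".

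The section on baseline and outcome data specifies a linear mixed-effects model with group, visit and their interaction. It names no analysis population. Nowhere does the article say that low compliers stay in the primary comparison, or that the 70% threshold serves only a secondary analysis.

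**The concern.** Randomisation makes the two groups comparable at the start. A rule that changes a participant's status on the basis of pill-taking afterwards can undo that, because pill-taking may be linked to the outcome and may be affected by treatment. The safety section itself anticipates nausea, vomiting, fatigue and allergic reaction, any of which could lower pill-taking more in one arm than in the other.

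This is not a complaint that an analysis population is missing, which a condensed article may leave to a fuller document. The article states a rule. An analysis plan that follows it would carry the problem, and one that keeps everyone would depart from the natural meaning of the rule.

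The effect estimate is at stake. The Background section says that the results will inform the design and sample size of a larger trial, so an estimate shifted by selection, or one that describes compliers only, could carry forward into that calculation.

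**Working it through.** **1. The plan's own figures.** The Sample size section gives the target: "5.0 square millimeters is assumed a clinically relevant difference between the two groups". It also gives SD 6.85, a 5% significance level and 80% power. The Randomization section gives "The allocation ratio will be 1:1 in blocks of 2".

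- Formula: n per group = 2(z_α + z_β)² SD² / Δ².
- One-sided 5%: 2 × (1.645 + 0.842)² × 6.85² / 5.0² = 23.2, rounded up to 24. Total 48, and 48 / 0.8 = 60. Both stated figures reproduce.
- Two-sided 5%: 2 × (1.960 + 0.842)² × 6.85² / 5.0² = 29.5, rounded up to 30 per group, or 75 in total after inflation. This does not reproduce.

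The unstated sidedness is a separate matter. What counts here is that 60 × 0.8 = 48 = 2 × 24: in planning, the required number is what remains after drop-outs are taken away.

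**2. Size of a possible bias, by formula.** Assumptions, not in the documents: no true effect; 20% removed from each arm (30 falls to 24); in the CKJ arm only, the wheal of those removed would have been 0.5 SD larger than that of those retained.

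- Gap = 0.5 × 6.85 = 3.425 mm².
- Shift in the CKJ mean = fraction removed × gap = 0.20 × 3.425 = 0.685 mm², and 0.685 / 5.0 = 14% of the target.
- SE = 6.85 × √(1/24 + 1/24) = 1.977 mm², so the shift is 0.685 / 1.977 = 0.346 SE.
- Two-sided type I error at nominal 5% = P(Z > 1.960 − 0.346) + P(Z < −1.960 − 0.346) = 0.053 + 0.011 = about 6.4%.

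**3. Check by simulation.** 30 per arm, SD 6.85, no true effect, two-sample t test at two-sided 5%, with participants removed on a compliance variable correlated with the outcome. Removal rates and correlations are again assumptions. Negative bias favours CKJ.

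| Removed (CKJ / placebo) | Correlation with outcome (CKJ / placebo) | Bias, mm² | Type I error |
|---|---|---|---|
| 20% / 20% | 0 / 0 | about 0 | 5.0% |
| 20% / 20% | 0.3 / 0.3 | about 0 | 4.9% |
| 20% / 20% | 0.3 / 0 | −0.73 | 6.5% |
| 20% / 20% | 0.5 / 0 | −1.20 | 9.0% |
| 30% / 10% | 0.3 / 0.3 | −0.63 | 6.1% |
| 30% / 10% | 0.5 / 0.5 | −1.04 | 8.5% |

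The third row agrees with step 2. Bias needs a difference between the arms, either in how non-compliance relates to outcome or, where it does relate, in how often it occurs. Reversing the sign of the relation reverses the direction of the bias.

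**4. Can the mixed model repair this?** Table 1 schedules the skin prick test at screening and week 12 only. A participant left out at week 12 has no other post-randomisation value of the primary outcome. The model could use only the pre-treatment value, and so could correct only for what that value predicts.

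**5. What keeping everyone costs.** Assume that 20% of the CKJ arm comply poorly and gain between 0 and 70% of a 5.0 mm² effect. The difference as randomised is then 0.8 × 5.0 + 0.2 × 0 = 4.0 mm² to 0.8 × 5.0 + 0.2 × 3.5 = 4.7 mm². With all 30 per arm, power is 0.73 to 0.84 one-sided (0.62 to 0.76 two-sided). With 24 per arm and the full 5.0 mm², it is 0.81 (0.72).

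**The case against.** The strongest reply is that the article never says that these participants' data are deleted, that they miss the week-12 test or that they leave the model. Inflating for dropout is also normal in trials that analyse everyone as randomised, and the Discussion speaks of assessing the effect in 60 volunteers. This stands in part: removal is an inference from the word used, its place under Statistical analysis and the inflation. It does not clear the rule, since nothing keeps low compliers in, and the remark in the Discussion does not define an analysis set.

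Three stronger readings are tempting, and the document does not support them.

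- **That the rule removes people from the active arm only**, because it names CKJ pills. The Randomization section conceals allocation from those who would count the pills, so they could not apply it to one arm. The safety section uses the same expression when it plainly means the study pills of every participant.
- **That the comparison is biased.** The simulation gives about zero when non-compliance is unrelated to outcome or acts alike in both arms. The documents offer no evidence of a difference between arms, and the trial is double-blind.
- **That participants who tolerate CKJ poorly vanish from the trial.** Table 1 schedules adverse-event monitoring at every visit after baseline, and nothing limits safety reporting to compliers.

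A gap between 5.0 mm² in compliers and 4.0 mm² as randomised would also be a difference between two questions, not selection bias.

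**Conclusion.** The point holds as a badly fixed rule that leaves the primary comparison open to bias of unknown size and direction. Under the stated assumptions (20% removed, 0.5 SD gap in the CKJ arm only) the bias is about 0.7 mm², or 14% of the target, with two-sided type I error of about 6.4% to 6.5%. It is about zero if non-compliance is unrelated to outcome or acts identically in both arms. The document supplies neither the removal rate nor the gap; its 20% is a dropout allowance, borrowed here as a plausible fraction.

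The point should be corrected, but it is not among the gravest. The Background calls the trial a first pilot, and the Discussion leaves the confirmatory conclusion to a later full-scale trial.

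**What to change.** Replace the rule in the Compliance section. State that every randomised participant has the week-12 skin test and blood draw whatever the pill count, and is analysed in the assigned group; make this the primary analysis. Use compliance above 70% of study pills, counted identically for CKJ and placebo, only to define a supportive per-protocol analysis. Reserve the term drop-out for participants whose week-12 outcome cannot be obtained, so that the 20% allowance covers missing outcomes alone.

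The cost is a change of wording and the effort of bringing low compliers back at week 12. The primary estimate may be somewhat diluted by poor compliers: by 0.3 to 1.0 mm² under the assumptions above, and by less if fewer than 20% comply poorly.

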#### Sample size

Sample size calculation is performed; primary outcome measure will be the histamine-induced wheal size, whereby 5.0 square millimeters is assumed a clinically relevant difference between the two groups, with a standard deviation of 6.85, alpha set on 5% and power on 80%. This resulted in a required number of 24 subjects in each group. Assuming a dropout rate of 20%, a total of 60 subjects will be enrolled in this trial.

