### Statistical analysis

#### Baseline data and Outcomes data

Statistical analysis will be performed using SAS version 9.0 for Windows (SAS Institute, Cary, NC, USA). Data will be presented as mean±SD values. The Chi-square test will be performed to determine differences at baseline in frequencies of categorized variables between the groups. A linear mixed-effects model will be applied to repeated-measures data for each continuous outcome variable. Fixed effects will be included treatment group, treatment visit, and interaction between treatment group and visit. When the analysis of variance indicated significant differences among groups, *post hoc *test (Turkey's test) will be used to separate the differences between groups before and after the 12-week intervention period. A value of p < 0.05 will be considered statistically significant.

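### The 24 per group gives the stated 80% power only with an undeclared one-sided 5% test; under the planned non-directional analysis at p < 0.05 the power is about 70%.

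*Protocol article*

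**What the plan says.** The Sample size section of the protocol article names histamine-induced wheal size as the primary measure. Its inputs are:

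- Difference: "5.0 square millimeters is assumed a clinically relevant difference between the two groups".
- Variability: "with a standard deviation of 6.85".
- Error rates and result: "alpha set on 5% and power on 80%. This resulted in a required number of 24 subjects in each group".

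It then allows for 20% dropout and arrives at 60 enrolled. The Randomization section gives equal allocation: "The allocation ratio will be 1:1 in blocks of 2".

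The analysis is set out under Baseline data and Outcomes data. It is a linear mixed-effects model with group, visit and their interaction, followed by a Tukey post hoc test, conditional as follows: "When the analysis of variance indicated significant differences among groups". The threshold is: "A value of p < 0.05 will be considered statistically significant". Neither section says whether the 5% is one-sided or two-sided, and no other section declares a one-sided test.

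**The concern.** All the inputs for a two-sample comparison of means are given except the sidedness of alpha. Under the usual two-sided reading they do not lead to 24 per group. They do so under a one-sided reading, which the protocol never declares and which does not fit F-tests and Tukey comparisons.

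What is at stake is the power claim. If the sample size was computed one-sided and the analysis is non-directional, the risk of missing a true 5.0 mm² effect at the planned evaluable number is about 30%, where the protocol implies 20%. Anyone relying on the stated 80% would give a null result more weight than it deserves. The Background and Discussion also present this trial as the basis for designing a larger RCT, including its sample size, so the planning calculation should be one that can safely be reused.

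**Working it through.** **Inputs.** Difference 5.0 mm², SD 6.85, alpha 0.05, power 0.80, dropout 20% (Sample size); 1:1 allocation (Randomization).

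Standardised effect: d = 5.0 / 6.85 = 0.730, so d² = 0.5328.

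**Step 1. Reproduce the protocol's 24.**

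Normal approximation, n per group = 2(z_α + z_β)² / d², with z_β = 0.8416.

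- One-sided 5% (z_α = 1.645): 2 × (1.645 + 0.8416)² / 0.5328 = 23.2, so 24.
- One-sided 5% with the t distribution (noncentral t): 23.9, so 24.

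The dropout step is also right: 24 / 0.8 = 30 per group, 60 in total.

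**Step 2. The same inputs, two-sided.**

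- Normal approximation (z_α = 1.960): 2 × (1.960 + 0.8416)² / 0.5328 = 29.5, so 30.
- t distribution: 30.45, so 31.

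The gap from 24 is 6 to 7 per group, at least a quarter of the stated number, so rounding does not explain it.

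**Step 3. Power at the protocol's numbers.**

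Noncentrality at 24 per group = d√(n/2) = 0.730 × √12 = 2.53, with 46 degrees of freedom. The critical value is 2.013 two-sided and 1.679 one-sided.

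| Evaluable per group | Two-sided 5%, t-test | One-sided 5%, t-test |
|---|---|---|
| 24 (after 20% dropout) | 69.7% | 80.1% |
| 30 (no dropout) | 79.4% | 87.5% |
| 31 | 80.7% | 88.4% |

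The normal approximation gives two-sided power of 71.5% at 24 and 80.7% at 30.

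**Step 4. Detectable difference at 24 per group, 80% power, two-sided.**

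- t distribution: 5.66 mm².
- Normal approximation: (1.960 + 0.8416) × 6.85 × √(2/24) = 5.54 mm².

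**Step 5. Enrolment that would keep 80% power for 5.0 mm², two-sided.**

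- t-test: 31 / 0.8 = 38.75, so 39 per group, 78 in total.
- Normal approximation: 30 / 0.8 = 37.5, so 38 per group, 76 in total.

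**The case against.** The strongest reply has four parts.

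*Sidedness is not stated, and the aim is directional.* The objectives ask whether the pills reduce the skin response, and the Discussion expects suppression, so a one-sided test may have been intended. It is true that two-sidedness is inferred here rather than quoted. But a directional hope does not set a one-sided alpha, and a one-sided sample size would still conflict with the F-tests and Tukey comparisons in the analysis section. The text needs changing on either reading.

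*Sixty are enrolled, so power is close to 80%.* That holds only if nobody is lost. The protocol itself assumes 20% dropout and calls 24 the required number. Its Compliance section also counts anyone at 70% compliance or below as dropped out. The range of about 70% to 79% is fair to report, with 70% applying at the planned evaluable number.

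*A repeated-measures analysis using baseline could be more powerful than a plain t-test.* This is possible. If 6.85 is an unadjusted SD, adjustment for baseline would restore two-sided 80% power at 24 per group given a baseline-to-follow-up correlation of about 0.43 (normal approximation) to 0.47 (t-test). The protocol gives no correlation, does not say which SD 6.85 is, and does not present 24 as an adjusted figure. So this does not explain the 24, although 70% should be read as the power of the unadjusted comparison.

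*It is a pilot, and confirmation is deferred to a larger trial.* This stands in part. Type I error and the treatment estimate are unaffected, and the SD observed here will not be distorted by the planning error. The protocol nevertheless makes a formal power claim, and that claim should be correct.

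**Conclusion.** The point holds. The stated 24 per group is a one-sided 5% calculation, while the planned tests are non-directional at p < 0.05. For a true difference of 5.0 mm² with SD 6.85, power at 24 evaluable per group is 69.7% rather than 80%, and it stays just short of 80% (79.4%) even with no dropout. The two-sided requirement is 31 per group.

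This rests on three things: the protocol's own difference and SD; an unadjusted two-sample comparison; and reading the analysis as two-sided, which follows from the tests named and the absence of any one-sided declaration.

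**What to change.** Keep 60 participants and replace the power statement in the Sample size section with wording such as: *With 24 evaluable participants per group, a two-sided alpha of 5% and an SD of 6.85 mm², the power to detect a difference of 5.0 mm² is about 70%; the difference detectable with 80% power is 5.7 mm².* State in the analysis section that the primary test is two-sided. The cost is one paragraph and a less favourable stated power, with no extra participants.

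Adjusting the primary comparison for the baseline wheal could recover part of the shortfall without more participants. How much depends on a correlation the protocol does not give, so no gain should be claimed until that value is stated and supported.

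There are two alternatives. The sponsor could enrol 78 (39 per group) to keep 80% power for 5.0 mm² with a two-sided test, at a cost of 18 more participants. Or it could declare and justify a one-sided 5% test and rewrite the analysis section to match, which would leave 24 and 60 unchanged but needs a defensible reason for testing in one direction only.
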